## Discussion

The DI_SOUND study is designed to develop and validate a digital classifier of neonatal cardiac sounds with the aim of improving the efficiency and effectiveness of screening for SHD in newborns. Current neonatal cardiovascular screening strategies rely on pulse oximetry (pre- and post-ductal oxygen saturation) combined with physical examination prior to discharge.^12–16^ While this approach has improved early detection of critical congenital heart disease, its diagnostic performance remains suboptimal, particularly in terms of sensitivity and operator dependency.^16^

Cardiovascular auscultation, historically a cornerstone of neonatal assessment, is inherently subjective and dependent on clinician experience.^14^ Several contemporary factors further limit its effectiveness. First, increasing prenatal detection of SHD has led to centralization of care, reducing exposure of general paediatric trainees and frontline providers to pathological cardiac findings, thereby potentially diminishing auscultatory proficiency.^35^ Second, early postnatal discharge (typically within 48–72 h) may occur before the full haemodynamic expression of certain defects, particularly those involving post-tricuspid shunts, due to persistently elevated pulmonary vascular resistance during transitional circulation. Third, the growing reliance on advanced diagnostic technologies may paradoxically reduce emphasis on meticulous physical examination skills.^35^ Collectively, these factors contribute to the persistence of false-negative screening results, which carry significant clinical risk.

Conversely, current screening strategies are also limited by suboptimal specificity, leading to a considerable number of false-positive cases. This results in unnecessary cardiology referrals, increased healthcare utilization, prolonged hospitalization, and heightened parental anxiety. Therefore, there is a clear unmet need for tools that can enhance both sensitivity and specificity while remaining accessible and scalable.

Within this context, the development of a digital heart sound classifier represents a potentially transformative approach. By leveraging signal processing and machine learning techniques, such a tool may provide objective, reproducible, and operator-independent assessment of cardiac sounds. Importantly, the integration of this technology into widely available digital health and telemedicine platforms could facilitate large-scale deployment, including in low-resource settings where access to specialized neonatal and cardiology expertise is limited.^36^ In such environments, improved early detection of SHD could have a particularly profound impact, as delayed diagnosis is often associated with worse clinical outcomes and limited treatment options.^36^

From a health economics perspective, enhancing early detection of critical, often ductal-dependent, heart defects are highly cost-effective, given the substantial gains in quality-adjusted life years associated with timely intervention—even in resource-constrained healthcare systems.^37^ Thus, improving screening performance is not only clinically relevant but also aligned with broader public health priorities.^38,39^

At the same time, it is important to acknowledge that the implementation of artificial intelligence–based diagnostic tools does not automatically translate into improved clinical outcomes.^40^ Recent evidence suggests that the real-world effectiveness of such technologies depends on multiple factors, including data quality, integration into clinical workflows, user acceptance, and appropriate validation across diverse populations.^40^ Accordingly, the DI_SOUND classifier should be viewed as a complementary tool rather than a replacement for existing screening strategies, with its ultimate value to be determined through rigorous prospective clinical validation. Our ultimate goal is that the DI_SOUND classifier will undergo clinical validation to work as a scalable algorithm for any commercially available telemedicine platform. We believe that a tool easily implementable in commercially available digital health care platforms may have a substantial positive impact in the management of newborns with SHD. Improving screening sensitivity will reduce the number of ‘false negative’ screening results with a potential major impact on patient safety, prognosis, patient care, hospital logistics and this effect may be even more pronounced in low-income setting such as developing countries or remote areas with challenging access to tertiary referral centres, and longer transportation time.^39^ Better screening specificity will reduce the number of ‘false positive’ results with positive effect on health-care cost, reduce family anxiety and newborn discomfort. More importantly, a digital classifier can be easily implemented into tele-medicine web-based platform optimizing screening scalability, penetration, and real-world efficiency.

In summary, this study addresses a clinically significant gap in neonatal cardiovascular screening by proposing an innovative, scalable, and potentially cost-effective solution. If successfully validated, this approach may enhance early detection of SHD, optimize resource utilization, and improve neonatal outcomes, particularly in settings where current screening practices are limited by expertise and infrastructure.

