## Study aims

Aim 1: Develop a binary classifier for normal vs. abnormal cardiac sounds in newborns.

Aim 2: Validate the binary classifier in a consecutive, independent cohort of newborns.

Aim 3: Cost-effective analysis of digital vs. standard screening modality for CHD in newborns.

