Concordance/discordance pattern between patient-centred comparisons between digital and clinical screening results will be performed using the echocardiography as primary modality of outcome ascertainment (*Figure 1*). False positive will be defined healthy newborns receiving a ‘positive’ screening result using either the clinical (standard or face-to-face auscultation) or the digital approach. Similarly, false negative will be defined newborns with SHD receiving a ‘negative’ screening result using either the clinical (standard or face-to-face auscultation) or the digital approach.

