**Figure 1 ztag103-F1:**
[figure not shown]
Diagram of validation phase. Each newborn with blinded cardiovascular status will undergo clinical screening as indicated by current practice and regulations and digital screening using the DI_SOUND algorithm. Gold standard evaluation will be comprehensive echocardiography. Pertinent diagnostics are reported at the bottom.

Cost-effectiveness validation (Aim 3)

Aim 3 will evaluate the potential impact of digital screening on healthcare utilization and costs compared with current standard clinical screening. The target population will consist of newborns at low risk for SHD, with no prior indication for cardiovascular examination, in order to approximate the prevalence of undiagnosed cardiovascular abnormalities in the general newborn population.

For the purpose of this analysis, outcomes will be explicitly defined as follows:

Prevented unnecessary examinations: cases in which (healthy) newborns with a positive result at standard clinical screening but a negative result at digital screening are subsequently confirmed to be free of SHD (i.e. false positives avoided by digital screening).Missed necessary examinations: cases in which newborns (with SHD) with a positive result at standard clinical screening but a negative result at digital screening are subsequently diagnosed with SHD (i.e. false negatives introduced by digital screening).

A decision-analytic modelling framework will be developed to compare digital screening with standard clinical practice. Model inputs will include estimates of SHD prevalence, test performance characteristics (sensitivity and specificity of both screening strategies), and downstream diagnostic pathways. Cost estimates will be derived from national diagnosis-related group reimbursement schedules to reflect healthcare system expenditures associated with confirmatory examinations and missed diagnoses.

To account for parameter uncertainty and variability, a probabilistic sensitivity analysis will be conducted using Monte Carlo simulation. This approach will allow repeated sampling from predefined distributions of key parameters (e.g. prevalence, sensitivity, specificity, and costs) to generate distributions of expected costs and outcomes for each screening strategy. The primary outcome will be the incremental cost-effectiveness of digital screening compared with standard clinical screening, expressed in terms of cost per unnecessary examination avoided and cost per missed SHD case.

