Net classification improvement will be used as the major statistical analysis for Experimental Aim 2, using ‘standard of care’ screening modality as comparison group. Sensitivity, specificity, positive, and negative predictive values will be calculated, and likelihood ratio will be analysed. C-statistics will be used to compute diagnostic performance of newly validated algorithm. Bootstrapping will be used to generate confidence intervals.

For experimental design Aim 2, sample size calculation is being presented for sensitivity. Assuming a two-sided α of 0.05% and 90% power, and a disease prevalence of 1% consistent with prior newborn CHD screening studies, we based our calculation on methods for diagnostic test evaluation. Specifically, targeting a sensitivity of approximately 90% with a desired confidence interval width of ±10%, at least 19–20 cases of CHD are required. Given the low expected prevalence (1%), this corresponds to a total sample size of approximately 1900–2000 newborns. This approach is consistent with previously published recommendations for validation of diagnostic algorithms in low-prevalence settings.^34^ Accordingly, an independent validation cohort of approximately 1900 consecutively enrolled participants will be used.

Data will be reported as mean ± standard deviation, median (first and third quartile) or frequency (%). All tests were two-sided. A *P*-value <0.05 was considered significant. Standard statistical analysis will be performed using STATA® 17 h Release data analysis software (StataCorp LP, College Station, TX).

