## Limitation

The most notable limitation is the absence of reliable data to calculate power for the development/training phase. Second, some severe SHD (among others transposition of the great arteries with intact ventricular septum) may have minimal acoustic correlates, and, therefore, our approach may be of limited efficiency for these lesions. Third, clinical screening modality integrates a variety of non-acoustic information, such as general newborn appearance, breathing pattern, femoral pulses, oxygen saturation. It is possible that clinical screening method may outperform digital screening for specific subsets of congenital lesions. Fourth, the frequency response of the digital stethoscope may change significantly between stethoscope models, and this may affect the ability of the classifier to transfer performance to a different model. To mitigate this aspect, we have decided to disable all digital filtering and equalization upon sound acquisition. Development and validation of diagnostic tool in a specific world region may constitute *per se* a limit affecting world-wide generalizability. Lastly, small/premature neonates (<1.5 kg) were not included in the target population of our study by design. This neonatal population routinely undergoes comprehensive cardiovascular evaluation, including echocardiographic screening, which reduces the potential added value of a digital heart sound–based screening tool in this subgroup. They frequently present with clinical and physiological conditions (such as mechanical ventilation, underlying lung disease, haemodynamically significant patent ductus arteriosus, and pulmonary vascular abnormalities) that may introduce substantial acoustic variability and confound heart sound recordings. These factors would limit both the reliability of data acquisition and the generalizability of a classifier intended for the broader neonatal population. Fifth, we are aware that a specificity of 90% may be considered lower than expected for a screening test, however, few consideration should be made to this regard: (i) specificity for current clinical screening modality is reported to be between 95% and 99% with a much lower sensitivity (70–80%) and (ii) our boundary condition is assumed under worst case scenario but we aim for a significantly higher specificity and in the Supplementary material online, *Table S3* of the Online Supplementary Material we are reporting a summary table for diagnostic performance of our classifier under different scenarios showing a sustainable workload for lower specificity compared with optimal specificity (about 80 false-positive newborns every/1000). Finally, given the clinical fragility of preterm infants, we carefully considered the ethical implications of additional handling and sensor application and examination, including potential risks of infection and discomfort.

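### The Discussion presents the classifier as an add-on, but the stated contrasts set digital against clinical screening, and neither Aim 3 outcome counts what adding it would change

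*Protocol article*

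**What the plan says.** **Intended role.** The Discussion states that the classifier is to be seen as a "complementary tool rather than a replacement for existing screening strategies". The Limitation section gives a reason: some severe lesions have little acoustic signature, and clinical screening draws on saturation, pulses and appearance. It concedes: "It is possible that clinical screening method may outperform digital screening for specific subsets of congenital lesions".

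**Stated contrasts.**
- Study aims, Aim 3: "Cost-effective analysis of digital vs. standard screening modality for CHD in newborns".
- Validation phase (Aim 2): "Concordance/discordance pattern between patient-centred comparisons between digital and clinical screening results will be performed", with echocardiography as reference. False positives and false negatives are defined by a "screening result using either the clinical (standard or face-to-face auscultation) or the digital approach", so each approach has its own errors and no combined result is defined.
- Statistic plan: "Net classification improvement will be used as the major statistical analysis for Experimental Aim 2", with standard-of-care screening as the comparison group.
- Cost-effectiveness validation (Aim 3): "A decision-analytic modelling framework will be developed to compare digital screening with standard clinical practice". Two outcomes are defined. The first is healthy newborns positive clinically but negative digitally (examinations prevented). The second is newborns with structural heart disease (SHD) who are positive clinically but negative digitally (examinations missed).

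**The concern.** A tool meant to work alongside existing screening is judged by what changes when it is added: how many more affected newborns are found, and how many more healthy ones are referred. A head-to-head comparison answers a different question and can mislead in either direction. A digital screen no better overall than clinical screening may still find cases that clinical screening misses. One that looks better head to head may bring many extra referrals when added.

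The Discussion's main safety claim is a fall in false negatives. In an add-on use, that fall lies entirely among newborns who are clinically negative and digitally positive. Aim 3 defines no outcome for them, so its cost-effectiveness result would describe substitution while the article recommends addition.

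**Working it through.** **1. Which cells each use depends on.** Cross the two screens within each echocardiographic status.

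| Clinical | Digital | Changed by replacement? | Changed by adding (either positive)? | Aim 3 outcome? |
|---|---|---|---|---|
| + | − | yes | no | yes, both outcomes |
| − | + | yes | yes | no |

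Under an either-positive rule every clinical positive stays positive. Both Aim 3 outcomes are then zero by construction, and everything that changes lies in the row Aim 3 does not count.

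**2. Inputs.**
- Clinical screening: sensitivity 70–80%, specificity 95–99% (Limitation).
- Digital sensitivity: 90% (Statistic plan, Aim 2 sample size).
- Digital specificity: 90% (Statistic plan, Aim 1 target, given there as >90%). The Limitation section calls this its worst case.
- Cohort 1,900, prevalence 1% (Statistic plan). 1,900 × 0.01 = 19 with SHD and 1,881 without, which matches the plan's step from 19 cases to 1,900 newborns. Whether 19 cases give the stated precision is a separate matter and is not used here.
- Assumptions of this check: the either-positive rule and, in step 3, conditional independence of the two screens.

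**3. Under conditional independence.**
- Combined sensitivity = 1 − (1 − clinical)(1 − digital): 1 − 0.30 × 0.10 = 0.97; 1 − 0.20 × 0.10 = 0.98.
- Combined specificity = product of the two: 0.95 × 0.90 = 0.855; 0.99 × 0.90 = 0.891.
- Extra SHD cases = 19 × (1 − clinical sensitivity) × 0.90: 19 × 0.20 × 0.90 = 3.4; 19 × 0.30 × 0.90 = 5.1.
- Extra false positives = 1,881 × clinical specificity × 0.10: 1,881 × 0.95 × 0.10 = 179; 1,881 × 0.99 × 0.10 = 186.
- Total false positives: clinical alone 19–94; digital alone 188; combined 205–273.

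With digital sensitivity at the Aim 1 target of 95%, the extra cases are 19 × 0.20 × 0.95 = 3.6 to 19 × 0.30 × 0.95 = 5.4.

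**4. Without independence.** The share positive digitally and negative clinically is at least the excess of the digital over the clinical positive rate. It is at most the smaller of the digital positive rate and the clinical negative rate.
- SHD: lowest 19 × (0.90 − 0.80) = 1.9; highest 19 × (1 − 0.70) = 5.7.
- Healthy: lowest 1,881 × (0.10 − 0.05) = 94; highest 1,881 × 0.10 = 188.

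**5. Whether one contrast stands in for the other.** Take clinical 80%/99% and digital 90%/90%. Net classification improvement (change in sensitivity plus change in specificity) is:
- Replacement: (0.90 − 0.80) + (0.90 − 0.99) = 0.01.
- Addition, under independence: (0.98 − 0.80) + (0.891 − 0.99) = 0.18 − 0.099 = 0.08.

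The replacement figure suggests almost no net change. The add-on figure is made up of 18 points of sensitivity gained and 9.9 points of specificity lost. The first does not reveal the second.

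**The case against.** A reader might infer that the effect of adding the tool can never be obtained from this study. The documents do not support that. Both screens and echocardiography are done in every validation newborn, and the planned discordance table, split by SHD status, contains the clinically negative, digitally positive cells. What is missing is a named estimate built from them.

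A reader might also take the major Aim 2 analysis to be strictly digital alone against clinical alone. The Statistic plan names the comparator but does not say whether the new classification is digital alone or digital plus clinical, and net classification improvement can measure added value. The separate error definitions favour the head-to-head reading without settling it.

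The article fixes no combination rule, so the either-positive rule used here is only an illustration. The Aim 3 outcomes would also fit a use in which digital screening is applied only to clinical positives. The text does not state that use, and it could not reduce false negatives as the Discussion promises. Equally, an either-positive rule cannot raise specificity above that of clinical screening, which the Discussion also hopes to improve. This uncertainty is itself a reason to state the role.

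The size is soft as well. Auscultation is part of clinical screening, so the two results are plausibly correlated, and 90% specificity is a declared worst case. Finally, establishing stand-alone accuracy first is a legitimate design, and the full protocol in the supplement is not shown. Neither removes the conflict between the Discussion and the contrasts that the article itself fixes.

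**Conclusion.** The point holds as an inconsistency between declared role and stated contrasts. It is firmest for Aim 3, where the model has two strategies and both outcomes presuppose that a negative digital result overrides a positive clinical one. For Aim 2 it is narrower: the data and the cross-table are there, but no combined strategy or estimate of its effect is named.

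Under an either-positive rule the uncounted effect is about 3.4–5.1 extra SHD cases and 179–186 extra false positives per 1,900 newborns, assuming conditional independence. Without that assumption it is 1.9–5.7 and about 94–188. The false-positive figures rest on the worst-case specificity and would fall if specificity is higher.

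The material does not support a claim that the study cannot inform add-on use, or that the combined comparison must be co-primary. A second main hypothesis would rest on a few discordant newborns among about 19 cases.

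**What to change.** - Reconcile the Discussion with Study aims, Validation phase (Aims 2 and 3) and Statistic plan. State the intended role of the tool and how the clinical and digital results combine. The investigators must choose that rule.
- Keep the head-to-head comparison, and say which classification the net classification improvement refers to.
- In Aim 2, add a secondary descriptive comparison of combined against clinical screening alone. Report additional SHD cases and additional false positives per 1,000 low-risk newborns, with paired intervals.
- In Aim 3, add the combined strategy as a third arm and count the clinically negative, digitally positive newborns as outcomes, with and without SHD.
- If replacement is what is being evaluated, say so and limit the conclusion to that.

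The cost is a little more analysis and no new data, since both screens and the reference are already obtained in every newborn. The intervals for additional cases will be wide because only about 19 SHD cases are expected, and the report should say so.

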## Limitation

The most notable limitation is the absence of reliable data to calculate power for the development/training phase. Second, some severe SHD (among others transposition of the great arteries with intact ventricular septum) may have minimal acoustic correlates, and, therefore, our approach may be of limited efficiency for these lesions. Third, clinical screening modality integrates a variety of non-acoustic information, such as general newborn appearance, breathing pattern, femoral pulses, oxygen saturation. It is possible that clinical screening method may outperform digital screening for specific subsets of congenital lesions. Fourth, the frequency response of the digital stethoscope may change significantly between stethoscope models, and this may affect the ability of the classifier to transfer performance to a different model. To mitigate this aspect, we have decided to disable all digital filtering and equalization upon sound acquisition. Development and validation of diagnostic tool in a specific world region may constitute *per se* a limit affecting world-wide generalizability. Lastly, small/premature neonates (<1.5 kg) were not included in the target population of our study by design. This neonatal population routinely undergoes comprehensive cardiovascular evaluation, including echocardiographic screening, which reduces the potential added value of a digital heart sound–based screening tool in this subgroup. They frequently present with clinical and physiological conditions (such as mechanical ventilation, underlying lung disease, haemodynamically significant patent ductus arteriosus, and pulmonary vascular abnormalities) that may introduce substantial acoustic variability and confound heart sound recordings. These factors would limit both the reliability of data acquisition and the generalizability of a classifier intended for the broader neonatal population. Fifth, we are aware that a specificity of 90% may be considered lower than expected for a screening test, however, few consideration should be made to this regard: (i) specificity for current clinical screening modality is reported to be between 95% and 99% with a much lower sensitivity (70–80%) and (ii) our boundary condition is assumed under worst case scenario but we aim for a significantly higher specificity and in the Supplementary material online, *Table S3* of the Online Supplementary Material we are reporting a summary table for diagnostic performance of our classifier under different scenarios showing a sustainable workload for lower specificity compared with optimal specificity (about 80 false-positive newborns every/1000). Finally, given the clinical fragility of preterm infants, we carefully considered the ethical implications of additional handling and sensor application and examination, including potential risks of infection and discomfort.
